#### Exercise professionals

##### Course comprehension test

An anonymous course comprehension test will be administered immediately following course completion as a manipulation check. The test will include 10 multiple-choice questions with five response options each (e.g., “When a client says they decided to train in order to ‘lose belly fat,’ the most evident type of motivational regulation is: (a) external regulation, (b) introjected regulation, (c) identified regulation, (d) integrated regulation, or (e) intrinsic motivation” and “Integrating hedonic principles into exercise supervision and prescription can be as simple as: (a) aligning training intensity with what is individually preferred and tolerated, (b) adjusting speed/cadence/load in order to experience pleasurable sensations, (c) selecting activities/exercises/classes that are individually perceived as fun and enjoyable, (d) all of the above are correct, or (e) all of the above are incorrect”). Items are designed not only to assess recall but also to evaluate the ability to integrate and apply course content. Scores will be expressed as a percentage (0–100%), with incorrect answers penalized by deducting 1/5 of the value of each question.

##### Course-knowledge application test

During the four scheduled individualized sessions with professionals (T2 to T5; experimental groups only), participants will respond to two questions assessing the application of course content. These will be answered on 5-point Likert scales focused on (a) frequency (“How often do you use the knowledge or tools/strategies conveyed in the training course at the beginning of the season? 1 – Never; 5 – Always”), and (b) the degree (“To what extent do you translate the course content to your professional practice?; 1 – Superficially; 5 – Extensively”) of content application.

### Data management

Data will be collected and entered by the two researchers responsible for delivering the training courses. The final dataset will be anonymized and securely stored on a private server, in compliance with the General Data Protection Regulation (GDPR) of the European Union. Regular bimonthly checks will be conducted to ensure data quality and integrity. Access to the anonymized dataset can be requested from the primary investigator and will be considered upon review.

### Statistical methods

Preliminary analyses will be conducted prior to all statistical procedures to examine data quality, missingness patterns, and identify potential violations of statistical assumptions. All analyses are planned to be performed using SPSS v.27.0 (IBM, Co.). The primary outcome of the study is attendance, which will be analyzed both for all fitness center members and separately for those who joined the clubs after the commencement of the study (i.e., after September 1, 2025). Attendance will be operationalized as the individual’s mean weekly attendance within each three-month interval and assessed at four time points during the 12 months of the study (three, six, nine, and twelve months). Primary analyses of attendance will be conducted using linear mixed-effects models (LMMs), with time specified as a within-subject factor and individuals treated as random effects to account for repeated observations. Intervention condition (control, SDT-based training, and hedonic-based training), time, and their interaction will be included as fixed effects, with age and sex included as covariates. These models will be used to characterize and descriptively compare attendance trajectories over time across intervention conditions, with emphasis on the magnitude and direction of longitudinal patterns rather than on individual-level causal inference. Primary analyses will follow an intention-to-treat principle adapted to the cluster-allocated design, such that all eligible individuals are analyzed according to their fitness center’s assigned condition, regardless of attendance patterns or dropout. Linear mixed-effects models were selected because they incorporate all available longitudinal observations under a missing-at-random assumption without requiring imputation.

Because intervention allocation occurs at the fitness-center level and each condition is implemented in a single center, cluster-level variance and intraclass correlation coefficients cannot be estimated independently of condition-related effects. Accordingly, comparisons across intervention conditions are considered exploratory and descriptive in nature. For complementary descriptive purposes, 3 (Condition) × 4 (Time Points) split-plot ANOVAs may be conducted to summarize overall patterns of longitudinal change in attendance. Results from these analyses will be interpreted descriptively, given that intervention conditions are implemented at the fitness-center level.

Secondary outcomes include dropout and motivational variables. Dropout (membership cancellation) will be examined using administrative records from all members enrolling after September 1, 2025. Dropout rates will be summarized at three-month intervals, and time-to-event analyses will be used to describe adherence patterns over the 12-month period. Percentage attrition rates will be reported descriptively, and Kaplan–Meier survival curves will be used to illustrate the timing of dropout across conditions. Participants who remain actively enrolled at the end of the observation period will be treated as censored observations at their last available follow-up time point. Motivational and behavioral variables will be analyzed in the longitudinal subsample of participants. Changes over time in these variables (baseline, six, and twelve months) will be examined using linear mixed-effects models, with time specified as a within-subject factor and participants treated as random effects. Intervention condition, time, and their interaction will be included as fixed effects, with age and sex entered as covariates. Given the limited number of repeated measurements, models will be specified with a parsimonious random-effects structure. For consistency with prior literature and ease of interpretation, complementary 3 (Condition) × 3 (Time Points) split-plot ANOVAs may also be conducted, with results interpreted descriptively. Effect sizes will be reported as model-based estimates of change over time (e.g., differences in attendance slopes and estimated marginal means), with 95% confidence intervals. Additional control, complementary, and exploratory analyses are anticipated, particularly within ancillary studies.

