### Outcomes

The primary outcome variable will be club attendance, which, for the designated fitness centers, will only reflect club visits with the intent to exercise and not access complementary services (i.e., spa, well-being centers, coffee lounges). This will be assessed across all trimesters, with particular emphasis on one-year results (as the primary outcome endpoint). Comparisons will be made over time within and across intervention conditions for both new members enrolling between September 1, 2025, and August 31, 2026, and members already enrolled prior to this period, for whom the intervention may reflect a change from their prior club experience. The secondary outcomes will be behavioral (attrition rate, namely the number of membership cancellations or dropouts as a percentage of the total number of new members in a given time period; see Methods section for details) and motivational constructs (exercise habit, intention to be physically active, satisfaction of basic psychological needs, behavioral regulation, enjoyment, and affective exercise experiences), in line with the study’s secondary hypotheses regarding potential motivational and behavioral changes associated with the intervention conditions. These will be assessed in a subsample of participants who will voluntarily take part in the longitudinal evaluations. Additional variables (i.e., state self-control, intensity agreement, course content evaluation, one-year pre-intervention attendance, and attrition patterns at the club level, and the degree and frequency of application of the knowledge provided during the training course) will be included for descriptive or exploratory tertiary analyses. No harm is expected from the intervention.

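### As the mixed models are written, age and sex do essentially nothing to the slope (condition-by-time) contrasts, so any effect of age or sex mix on the rate of change stays in them

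*Protocol article*

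**What the plan says.** The Statistical methods section of the protocol article sets out the attendance model term by term: intervention condition, "time, and their interaction will be included as fixed effects, with age and sex included as covariates", with "individuals treated as random effects to account for repeated observations". Attendance is "assessed at four time points during the 12 months of the study (three, six, nine, and twelve months". The motivational models repeat the structure: "Intervention condition, time, and their interaction will be included as fixed effects, with age and sex entered as covariates". Condition-by-time is the only interaction named in either place.

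On reporting, the same section says: "Effect sizes will be reported as model-based estimates of change over time (e.g., differences in attendance slopes and estimated marginal means", with 95% confidence intervals. The Outcomes section looks across all trimesters "with particular emphasis on one-year results (as the primary outcome endpoint". The Objectives section words the primary hypothesis in terms of individual attendance trajectories over time. The Statistical methods section also acknowledges that "each condition is implemented in a single center" and therefore treats comparisons between conditions as descriptive.

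**The concern.** Two kinds of result will be reported: differences in change over time, and marginal means at given times. A person's age and sex, entered as single terms, shift that person's whole profile up or down by a constant. They can correct a comparison of levels. They cannot correct a comparison of changes, because the constant drops out.

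The trajectory comparison carries the primary hypothesis. Members are not individually allocated, each condition is one club, and the questionnaire subsample is voluntary, so age and sex mix may differ between conditions. If attendance falls faster at some ages or in one sex, clubs with different mixes will show different slopes with no training effect. A reader who sees age and sex listed as covariates could discount demographic mix as an explanation. For the slopes, that would be a mistake. The same applies to the motivational scales.

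**Working it through.** **Inputs from the protocol.** Fixed effects, covariates and the person random effect are as quoted above. Attendance has four time points and the motivational scales have three, with one club per condition. The plan gives no age or sex distribution by club and no relation of age or sex to attendance, so there is no plan figure for this point to reproduce. The only related figure is the subsample size, used below for cost. The repeated-measures calculation returns 53 completers (power 0.953), and 53 / (1 − 0.55) = 117.8, in line with the stated total of about 117.

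**Step 1: change contrasts.** Let the club-by-time means be free and let x be a person's covariate with coefficient β. With complete data, the fitted mean for club c at time t, evaluated at a common value x0, is

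adjusted mean(c, t) = raw mean(c, t) − β × (club mean of x − x0).

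The subtracted part does not depend on t. In the contrast [mean(c, 12) − mean(c, 3)] − [mean(k, 12) − mean(k, 3)] it cancels, whatever β is. Main effects of age and sex therefore leave the contrast exactly as it would be without them.

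**Step 2: what stays in the contrast.** Code the quarters 0 to 3. Suppose attendance depends on age through a level effect β and a trend effect γ per quarter per decade, and the clubs differ by D decades.

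- The level effect cancels.
- The trend effect leaves 3 × γ × D.

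The values of γ and D are assumptions, not protocol figures:

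- D = 1 decade: γ = 0.02 gives 0.06; γ = 0.05 gives 0.15; γ = 0.10 gives 0.30 visits/week.
- D = 0.5 decade: each figure is halved, so 0.03 to 0.15.
- D = 0 or γ = 0: nothing.

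**Step 3: the 12-month level.** The age difference at month 12 is (β + 3γ) × D. With complete data a single age term estimates the time average, β + 1.5γ, since the mean of 0, 1, 2, 3 is 1.5. What is left is 1.5 × γ × D, or 0.075 for γ = 0.05 and D = 1. With γ = 0 nothing is left, so the main effect adjusts the level fully.

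**Step 4: simulation check.** Random-intercept models were fitted to data with no true club effect: 3 clubs of 300 members, hedonic against control 10 years apart in mean age and 20 points apart in the share of one sex, and a level effect of 0.2 visits/week per decade. There were 5 replicates with complete data and 15 with dropout (56% incomplete). Figures are hedonic minus control, in visits/week.

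| Contrast | Scenario | No covariates | Main effects | Plus covariate-by-time |
|---|---|---|---|---|
| Change, 12 vs 3 months | level effects only, complete | 0.020 | 0.020 | 0.017 |
| | level effects only, dropout | 0.005 | 0.008 | 0.009 |
| | γ = 0.05, complete | 0.130 | 0.130 | −0.026 |
| | γ = 0.05, dropout | 0.154 | 0.155 | 0.024 |
| Level at 12 months | level effects only, complete | 0.242 | −0.003 | −0.008 |
| | level effects only, dropout | 0.238 | −0.004 | −0.005 |
| | γ = 0.05, complete | 0.450 | 0.147 | 0.076 |
| | γ = 0.05, dropout | 0.344 | 0.074 | −0.015 |

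For the change contrast, the largest gap between the first two models in any replicate was about 7 × 10⁻¹⁴ with complete data and 0.014 with dropout. With few replicates the averages carry sampling noise. In the complete-data row for the 12-month level, the useful figure is the difference between the last two columns, 0.147 − 0.076 = 0.071, against 0.075 from step 3. Late entry of new members during the year was not simulated.

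**The case against.** The strongest reply has four parts.

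1. **The article does not say that only main effects will be used.** It is condensed, and covariate-by-time terms could appear in a fuller plan. That is true. But the article states the fixed effects twice and names a single interaction, so a reader must take the model as given.

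2. **The comparisons are declared descriptive and club is confounded with condition.** This also stands: no covariate removes the confounding. It limits the benefit of the change, but it is no reason to leave in a part that is measured and removable.

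3. **The clubs were chosen to be alike.** The Trial setting section describes similar target clientele, and the Recruitment section cites standardized practices. This makes a large age gap less likely without excluding one, since no age or sex figures are given.

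4. **The covariates do useful work on the stressed one-year result.** They do, fully for level effects and partly otherwise, as the table shows.

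Two stronger readings are tempting, and the document supports neither. A reader might infer that every age and sex difference between clubs passes into the results in full. It does not: level effects cancel from change contrasts, and the main effects correct the 12-month means at least in part. A reader might also infer that the plan presents its results as adjusted for age and sex. The article only lists them as covariates and makes no such claim.

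**Conclusion.** The point holds in a limited form. Under the natural reading of the models, age and sex leave the slope contrasts unchanged with complete data and nearly so with dropout. This algebra needs no assumed figures. Bias remains in the slope differences only if two conditions are both met: age or sex affects the rate of change, and the clubs differ in age or sex mix. The 12-month marginal means are then only partly corrected, with half of the slope bias remaining in the complete-data case above.

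The size is unknown from the document. The range of 0.06 to 0.30 visits/week for a 10-year gap rests wholly on assumed values and shrinks in proportion to the gap. The change is worth making, but it does not alter the standing of the comparisons: with one club per condition they remain descriptive.

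**What to change.** In the Statistical methods section, add age-by-time and sex-by-time as fixed effects to the attendance models and the motivational models. Report the condition-by-time contrasts and the marginal means at each time point for one common, pooled age and sex distribution. If the terms are not added, state that slope differences are effectively unadjusted for age and sex.

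The change takes a couple of sentences and no new data. With time as a factor, the attendance models gain six parameters (2 covariates × 3), negligible with more than 2,000 members per club and about 200 new members per club in September alone. The motivational models gain four (2 × 2). That is a real but modest cost with about 53 completers, roughly 18 per club; the plain statement is a reasonable alternative there. By the article's own dates, follow-up ends in August 2026 and baseline data are not analyzed before the intervention period closes, so the terms could still be fixed in advance.

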## Objectives

The present study aims to examine the associations of two short, behavioral theory–driven professional training programs: one based on SDT and the other grounded in hedonic principles. The primary outcome of interest is health-club attendance over one year. In addition, the study seeks to examine associations with these programs on individual behavioral and motivational outcomes among exercisers. The primary hypothesis is that fitness centers implementing either theory-driven training program will exhibit more favorable individual attendance trajectories over time compared with the control condition. Furthermore, it is hypothesized that the hedonic training approach will be associated with higher attendance than the SDT-based intervention. This expectation is based on (a) the relative ease and immediacy with which the hedonic framework and its context-specific tools and strategies can be applied (Teixeira et al., 2024b) and (b) the theoretical premise that SDT-based behavior change requires a longer period for integration and internalization (Ntoumanis et al., 2021). Secondary hypotheses include the following: (a) both theory-driven interventions will be associated with lower attrition rates than the control group and (b) the interventions will be associated with favorable changes over time in behavioral and motivational constructs, including exercise habit, intention to be physically active, satisfaction of basic psychological needs, behavioral regulation, enjoyment, and positive affective experiences.

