As for the secondary outcomes, these will focus on (i) dropout rates at three-month intervals up until one year, and (ii) motivational variables. In the case of dropout rates, administrative records from all members enrolling after September 1, 2025, will be used. This outcome is derived from the complete population of new members during the intervention period, and the expected number of observed events over the 12-month follow-up is sufficient to support descriptive and time-to-event analyses of attrition patterns across intervention conditions. In the case of the motivational variables, the most restrictive analyses will be conducted in a subsample of exercisers enrolling in September. These participants will be recruited for the longitudinal assessment of behavioral regulation, satisfaction of basic psychological needs, exercise enjoyment, subjective exercise experience, exercise habit, and intention to be physically active, assessed at baseline, six months, and twelve months. Sample size considerations for this subsample were guided by the most restrictive planned within-participant longitudinal comparisons and estimated using G*Power (v.3.1.9.7) (Faul et al., 2009). Using benchmarks from a related work [e.g. (Teixeira et al., 2023; Andrade et al., 2022; Henriques et al., 2023)], a repeated-measures ANOVA assuming a small-to-moderate magnitude of change over time (*f* = 0.20), an *α* level of 0.05, statistical power (1-*β*) of 0.95, three repeated measurements, a correlation between repeated measurements of approximately r = 0.70, and allowing for potential violations of sphericity (*ε* ≈ 0.70), a minimum of approximately 53 participants completing follow-up assessments across the three fitness centers is expected to provide adequate sensitivity to characterize meaningful longitudinal changes in motivational outcomes over time. Linear mixed-effects models will be used for analysis, as they are expected to be at least as efficient as the repeated-measures assumptions used for these calculations and allow the inclusion of all available data in the presence of missing observations. Given that the average attrition rate in Portugal over a one-year period in these contexts has been reported as ranging between 50 and 60% (Pedragosa and Ferreira, 2024), a total sample of approximately 117 participants (≈55% attrition) will be required.

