##### Club attendance and attrition rate

Attendance data will be obtained through the electronic system that tracks the entrances and exits from the turnstile systems of the clubs. These data will be collected for the entire season (September – August) for all members, when the following condition is present: (a) active payment + (b) a minimum of 1 attendance per month^1^. The attrition rate will be calculated for each 3-month period and the entire season with the following formula: Attrition Rate = (Number of Cancellations or Dropouts / Total Number of Members) × 100. New club members who enrolled in the fitness clubs after September 1, 2025, will also be identified separately for subgroup analysis.

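### As written, the primary attendance model leaves out time when club attendance is known to be zero, so it estimates attendance as if members had stayed

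*Protocol article*

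**What the plan says.** All references are to the protocol article.

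- **Objectives:** "The primary outcome of interest is health-club attendance over one year". A secondary hypothesis expects lower attrition under both theory-driven trainings than under control.
- **Outcomes:** "The primary outcome variable will be club attendance, which, for the designated fitness centers, will only reflect club visits with the intent to exercise". The one-year result is the primary endpoint. New members may join up to 31 August 2026.
- **Club attendance and attrition rate:** this section names the source: "Attendance data will be obtained through the electronic system that tracks the entrances and exits from the turnstile systems of the clubs". The data are collected for the whole season for all members "when the following condition is present: (a) active payment + (b) a minimum of 1 attendance per month". The second condition carries a footnote marker; the footnote text is not in the copy reviewed.
- **Statistical methods:** the analysed value is each person's "mean weekly attendance within each three-month interval and assessed at four time points during the 12 months of the study". The model is a linear mixed model with condition, time and their interaction, and a random effect for the individual. The reason given is "Linear mixed-effects models were selected because they incorporate all available longitudinal observations under a missing-at-random assumption without requiring imputation". The same section says that everyone eligible is analysed under the condition of their club, "regardless of attendance patterns or dropout". A 3 × 4 split-plot ANOVA of attendance is optional.
- **Statistical methods, secondary outcomes:** membership cancellation is taken from administrative records and shown as rates and Kaplan–Meier curves.
- **Sample size:** the inflation step begins "Given that the average attrition rate in Portugal over a one-year period in these contexts has been reported as ranging between 50 and 60"%.

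**The concern.** The outcome is visits to the club, counted at the turnstile. Someone who has cancelled makes none, so the value is known. Under the collection rule, those intervals produce no attendance record. A mixed model fitted to the available records under missing at random then treats them as unknown and, in effect, projects them from the person's earlier visits and the condition's time course. The second collection condition does the same on a smaller scale: a paying member who stays away for a whole month fails it, so a true zero is removed because it is zero.

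The resulting estimate answers a different question from the stated one: how often members would attend if nobody left. About half of new members or more are expected to leave within the year, and the protocol expects leaving to differ by condition. What is removed is therefore large, and by the protocol's own hypothesis unequal between conditions. A training programme that worked mainly by keeping people enrolled would show almost nothing on the primary outcome.

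**Working it through.** **The plan's own figures.** The protocol gives no sample size or expected visit rate for attendance. Its one figure resting on attrition is the motivational subsample: 53 / (1 − 0.55) = 117.8, against about 117 stated (3 × 39). So the protocol itself plans on about 55% yearly loss.

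**Level at month 12.** Let *m* be mean weekly visits while a member and *a* the attrition by month 12. If leaving is unrelated to attendance,

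mean over all starters = (1 − *a*) × *m* + *a* × 0 = (1 − *a*) × *m*.

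The missing-at-random model targets *m*. *m* is not in the documents; 1.0 to 2.0 is assumed.

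| Assumed *m* | *a* = 50% | *a* = 55% | *a* = 60% |
|---|---|---|---|
| 1.0 | 0.50 | 0.45 | 0.40 |
| 1.5 | 0.75 | 0.675 | 0.60 |
| 2.0 | 1.00 | 0.90 | 0.80 |

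The ratio of 0.40 to 0.50 does not depend on *m*.

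**Check by simulation.** Assumptions: 400 members per condition, four quarters, 15 replicates, mean 1.5 visits per week while a member, between-person SD 0.7, within-person SD 0.5. Leaving was either unrelated to attendance or more likely after a low-attendance quarter (truly missing at random). The condition-by-time mixed model with a random person effect (age and sex omitted) was fitted with cancelled quarters missing, then with them set to 0. Month-12 means are in the order control / SDT / hedonic:

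| Attrition; visits while a member | Leaving | Cancelled quarters missing | Cancelled quarters = 0 |
|---|---|---|---|
| 55/55/55%; equal | unrelated | 1.48 / 1.51 / 1.51 | 0.69 / 0.69 / 0.69 |
| 55/55/55%; equal | low attenders leave sooner | 1.49 / 1.51 / 1.49 | 0.79 / 0.80 / 0.78 |
| 60/55/50%; equal | unrelated | 1.49 / 1.51 / 1.51 | 0.61 / 0.68 / 0.74 |
| 60/55/50%; equal | low attenders leave sooner | 1.49 / 1.53 / 1.52 | 0.71 / 0.82 / 0.87 |

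The planned model recovers the everyone-stays mean of about 1.5 in every row. With attrition of 60/55/50%, hedonic minus control is +0.02 to +0.03 from the planned model (1.51 − 1.49; 1.52 − 1.49) and +0.13 to +0.16 with zeros counted (0.74 − 0.61; 0.87 − 0.71). When low attenders leave sooner, the level ratio at 55% attrition is 0.79 / 1.49 = 0.53 rather than 0.45.

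**Sensitivity.** In further simulations with assumed visit rates and control retention of 39% (attrition 61%, just outside the protocol's range), a cancellation hazard ratio of 0.7 gave about +0.02 to +0.03 from the planned model and +0.13 to +0.17 with zeros counted. A ratio of 0.85 gave about +0.02 and +0.07 to +0.08. The direction is stable; the size follows the assumptions.

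**Zero-visit months.** Illustration: a paying member makes 2 visits per week in two months of a quarter and none in the third. Counting the third month gives 2 × 2/3 = 1.33 per week; leaving it out gives 2.0.

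**Split-plot ANOVA.** With ordinary listwise deletion it keeps only members with all four intervals. In the two equal-attendance scenarios where low attenders leave sooner, members still enrolled at month 12 averaged 1.74 to 1.80, against an everyone-stays mean of about 1.5.

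**The case against.** *The coding is not stated.* This stands in part. No sentence says that cancelled quarters are coded missing, and the footnote to the one-visit condition is not shown. The reading rests on the collection rule and the missing-at-random sentence taken together. It is still the natural one: no rule counts those quarters as zero, and turnstile data have little other missingness for the assumption to address.

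*Retention has its own outcome.* Attendance while a member, read beside retention, is a legitimate pair of targets, and which is primary is partly a design choice. But the protocol does not declare that target. It names one-year attendance, and the Kaplan–Meier curves do not correct the primary estimate.

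*The intention-to-treat sentence may govern only who is included and under which condition.* That reading is possible, so a reader who infers an outright contradiction goes too far. What remains is a mismatch between the stated outcome and what the model estimates.

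*Comparisons between conditions are declared exploratory,* with one club per condition. No confirmatory test hangs on the result, but a descriptive figure must still describe the quantity it is named for.

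A reader might also infer that most of the possible benefit is retention, or that the planned model will rank the conditions wrongly. The documents support neither. They make retention a large, hypothesised route, no more. A reversal can be constructed: with attrition 60% against 50% and assumed member attendance of 1.5 against 1.4, the while-a-member difference is 1.4 − 1.5 = −0.10 and the zero-counted difference is 0.50 × 1.4 − 0.40 × 1.5 = +0.10. That needs lower attendance among trained members, which nothing in the protocol predicts.

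**Conclusion.** The point holds. Read together, the collection rule and the primary model leave out time in which club attendance is known to be zero. The result describes attendance as if members had stayed, and largely misses any effect through retention. At the protocol's 50 to 60% attrition, the zero-counted month-12 mean is about 40 to 50% of the while-a-member mean if leaving is unrelated to attendance, and a somewhat larger share if low attenders leave sooner.

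The size of any distortion between conditions cannot be fixed from the documents, because visit rates and attrition by condition are not given. The simulated differences are illustrations. The conclusion also rests on the inferred coding; if the missing footnote or a fuller plan counts these intervals as zero, the article's wording needs correcting rather than the analysis.

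**What to change.** - **Outcome:** define primary attendance as visits per week per eligible member. Score as 0 both time after cancellation and zero-visit months of paying members, up to the earlier of 12 months from the member's start or the study end, 31 August 2026.
- **Late joiners:** leave time after the study end unobserved. A member who joins on 1 March 2026 has six observable months; the other six are not set to zero.
- **Collection rule:** amend the section on club attendance and attrition rate to match, so that neither ended payment nor a month without visits removes a member's record.
- **Model:** fit the condition-by-time model to this record with robust standard errors. These help with the many zeros, not with having one club per condition, a limit the protocol already acknowledges.
- **Supplementary:** keep the missing-at-random mixed model, labelled as attendance while a member, beside the Kaplan–Meier curves.
- **Split-plot ANOVA:** do not run it on only those members who have all four intervals.

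The cost is a changed extraction rule and revised analysis wording. Cancellation is already drawn from administrative records for new members; the same should be confirmed for existing members. Reported attendance levels will be lower, and the outcome will contain many zeros.
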